#### Exercises

With the described goals in mind, therapists can choose from four different exercises (see Figure 3). First, in the *in-phase *exercise patients move both hands simultaneously towards flexion followed by a movement towards extension. These movements should follow each other smoothly and rhythmically. Maximal flexion should occur at the moment of the metronome cue. The pacing frequency is set, so that the patient can easily complete the required 3 minutes of exercise time.

**Figure 3 F3:**
[figure not shown]
**Modified BATRAC exercises**. A: in-phase exercise with flexion of both hands on the cue. B: antiphase exercise with simultaneous right-handed flexion and left-handed extension on the cue for half of the antiphase exercises (vice versa for the other half). C: extension exercise with extension of hands on the cue. D: music exercise with tapping of both hands on the beat.

Second, in the *antiphase *exercise patients move both hands simultaneously to the left followed by a movement to the right. These movements should follow each other smoothly and rhythmically. Maximal flexion of the right hand and maximal extension of the left hand should occur at the moment of the cue in half of the exercises, and vice versa in the other half. Again, the frequency is chosen such that the patient can comfortably complete the 3 minutes exercise time.

Third is the *extension *exercise. Patients move both hands simultaneously towards extension; maximal extension should occur at the moment of the cue. In this exercise extension activity is emphasized, such that active movements towards flexion are not required: after each cued maximal extension, patients can relax the wrist extensors and let the hands fall back to a neutral position. Again, the patient should comfortably complete the 3 minutes of exercise time with the chosen frequency.

Finally, in the music exercise the manipulanda are not used; instead, the patient's hands are placed (palms down) on the table top between the armrests. Through the headphones patients will hear a song in which the beat, with a specific and constant frequency, is emphasized by slightly louder pitches. There are several songs to choose from with pacing frequencies ranging from 0.8 to 1.4 Hz. Patients are instructed to raise their fingers and hand, while keeping the base of the hand resting on the table, and tap the hand on the table on the beat of the music. This can be done either in-phase or in antiphase.

As stated above, in each exercise the pacing frequency is set at a frequency that allows the patient to comfortably complete the 3 minutes exercise time. Because metronome beats at frequencies below 0.67 Hz (and above 4 Hz) are not perceived as rhythmic patterns [69,70], a minimum frequency of 0.8 Hz is used in the exercises. To enhance the training effect, however, the actually used pacing frequency will be the highest possible comfortable frequency for each individual patient, and may be increased over the intervention sessions. Therapists are advised to vary the exercises during each session to enhance therapy compliance. However, in-phase exercises are prioritized over antiphase exercises. In-phase bimanual movement patterns are most stable [45] and are therefore assumed to benefit most from interhemispheric interaction [71,72]. Patients with difficulties to keep track of the pacing frequency are encouraged to facilitate the rhythmic movements, for instance by counting and foot tapping. Tempo, types of exercise, and performance will be recorded in a patient-log to keep track of the course during the 6-week intervention period. Patients are also advised to practice rhythmic bimanual exercises, like clapping to music beats, in their own time. (Figure 3.)

#### Feedback

The computer connected to the modified BATRAC-apparatus provides feedback about the patient's performance. During the exercise, a diagonal line in a left-hand position by right-hand position plot marks the ideal line of coordination. The actual movement is presented by a moving dot with a 4 cm trailing tail (see Figure 2B). In early stages of the intervention, this form of feedback is not presented to the patient during the exercise to avoid attentional interference. In later sessions, when the patient is accustomed to the exercise, this form of visual feedback will be used to improve bilateral coordination.

After each exercise, the maximal amplitudes towards flexion and extension of both hands, and the relative phase between both hands (Φ, [73]) and its variability are presented in numbers and diagrams (see Figure 2B). These are recorded in a patient-log and will be used to motivate the patient to improve performance in following exercises.

### Modified CIMT

Like the modified BATRAC group, the modified CIMT group receives 60-minute therapy sessions, 3 days a week for 6 consecutive weeks. Modified CIMT involves functionally oriented task practice of the paretic arm and hand, while the less-impaired hand is restrained for 6 hours each weekday, hence also during therapy.

#### Goals

Modified CIMT is aimed at progressively improving motor task performance of the paretic arm and hand. A premise for this improvement is the prevention or turnabout of learned non-use [29,74-78]. A specific goal is to increase control over active extension of wrist and fingers, as this ability is important for fine motor control in functional tasks [24,25].

#### Exercises/matrix

Modified CIMT techniques include repetitive functional task practices and shaping of the desired improvements of movement using the technique of successive approximation (i.e., breaking complex movements into steps) [74,76]. During exercise the patient receives continuous verbal feedback and stimulation and, if necessary, hands-on facilitation of movements.

The exercises follow a quasi-hierarchical bottom-up approach from more easy applied gross motor functions to more complex in-hand manipulations. Figure 4 represents the matrix that serves as a guideline for building-up the modified CIMT exercise program. In this matrix the trained functional movements are described at 4 functional levels: gross arm movements, grasps and grips, in-hand manipulations and fine motor control, and combinations of movements in ADLs. The matrix follows a hierarchical pattern. As can be seen in the matrix, there is no hierarchy within the third level. Preferably, patients should train on the highest possible level and engage exercises that demand the most of their possibilities. Task difficulty within each exercise is varied by adjusting spatial or temporal demands. The content and duration of each session as well as the shaping exercises are recorded in a patient-log reflecting the progress in reaching treatment goals. (Figure 4.)

**Figure 4 F4:**
[figure not shown]
**Quasi-hierarchical modified CIMT Matrix**. The matrix functions as a tool for therapists. Exercise difficulty increases from top to bottom and from left to right. Patients should train on their highest possible level.

#### Mitt

To encourage the use of the most affected arm and hand in ADLs, a padded safety mitt (Sammons Preston # 6727; Sammons Preston, Inc., Bolingbrook, IL, USA) is applied to immobilize the less affected hand for at least 6 waking hours each weekday. A therapist, nurse, or family member should help putting on and taking off the mitt. The mitt should be taken off during bathroom activities. Patients that go walking by themselves are only allowed to wear the mitt if they score more than 3 points on the Functional Ambulation Categories (FAC). The mitt prevents contracture with firm polyester filling and allows (preventive) elbow extension, leaving sufficient movement when needed, for example in case the patient threatens to fall.

### DMCT

DMCT is an exercise therapy based on existing guidelines for upper extremity treatment after stroke as presented by the Dutch Society of Occupational Therapy [79] and the Royal Dutch Society of Physical Therapy [80]. This exercise therapy is typically provided by therapists at the RCA. However, specific elements of (modified) BATRAC (e.g., rhythmic cues) and (modified) CIMT (e.g., use of mitt) will not be used.

Therapy will be provided 60 minutes per treatment session, 3 days a week for 6 consecutive weeks, and will not contain specific elements of the other two therapies. The content and duration of the sessions are recorded in a patient's log.

### Power analysis

The number of patients is based on a statistical power of 80% (preventing Type II error) with an alpha of 5% (preventing Type I error) for detecting a meaningful difference of 6 points on the ARAT as the primary measurement of outcome and expecting 15% drop-out. The statistical power for detecting 10% or 6 points difference between groups is based on the following power calculation:

(Z_1-α/2 _+ Z_1-β_)^2 ^= 10.43 (assuming an alpha of 0.017, corrected for multiple testing with 3 groups and a Beta of 0.80)

σ2 (expected variance of sample on ARAT) = 26

Δ2 (assumed difference in favour ARAT) = 36

r (expected ratio between intervention groups) = 1

Expected numbers needed per intervention group (N_per group_) = 15 (excluding expected drop out of less than 25%).

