### Outcome variables

The primary outcome variable will be the score on the Action Research Arm test (ARAT). Secondary outcome variables are the scores on the Motricity Index (MI) of the arm, Fugl-Meyer for the arm (FM-arm), Nine Hole Peg test (NHPT), Erasmus modification of the Nottingham Sensory Assessment (EmNSA), Motor Activity Log (MAL), and Stroke Impact Scale (SIS version 3.0). All assessments will be applied to all patients at t0, t1, and t2.

Non-parametric statistics for independent samples will be used [81]. A Kruskal-Wallis test will be used to examine whether improvements before and after intervention (from t0 to t1) were significantly different between the three intervention groups (i.e., BATRAC, CIMT, and DMCT). When a significant difference is found between the three groups, a *post-hoc *Mann-Whitney U test will be applied to reveal which groups (CIMT, BATRAC, or DMCT) differ significantly from each other. The same procedure will be used for observed changes after the 6 weeks retention period, i.e., from t1 to t2.

The ARAT is a valid, reliable, and responsive performance test [82] of the ability to perform gross movements and to grasp, move, and release objects differing in size, weight, and shape [83]. The minimal clinically important difference is set at about 10% of the scale's range, i.e., 6 points [84]; improvement by > 10 points is defined as return of dexterity [17].

The MI will be used to measure strength in upper extremities [85]. Higher scores represent greater strength in the upper limb. This instrument provides a reliable and valid assessment of the presence of paresis in stroke patients by testing 6 functions rated for each limb [64,85].

The FM arm score is a reliable and valid motor performance test consisting of 33 tasks performed by the affected upper limb [86,87]. The FM-arm test evaluates the ability to make movements outside the synergistic pattern. Performance on each task is rated as 0, 1, or 2, with higher rates representing better performance. The FM-arm measure will be used as the sum of 33 ratings (possible range 0 to 66 points).

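### Fifteen per group gives 80% power only for a large-sample z-test at alpha 0.017; at that level the planned Kruskal-Wallis and Mann-Whitney tests give about 70–72% at 15 analysed per arm and 75–78% at 17

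*Protocol article*

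**What the plan says.** All sizing inputs are in the Power analysis section of the protocol article. It opens with "The number of patients is based on a statistical power of 80"%, "with an alpha of 5% (preventing Type I error"), a 6-point difference on the ARAT, and "expecting 15% drop-out". The calculation itself uses a squared sum of normal quantiles of 10.43, "assuming an alpha of 0.017, corrected for multiple testing with 3 groups and a Beta of 0.80" (the last item is evidently power, not beta). The variance is given as "expected variance of sample on ARAT) = 26", the squared difference as 36 and the allocation ratio as 1. The result is 15 per group, "excluding expected drop out of less than 25"%. The Abstract and the Recruitment section set the total at sixty patients, so 20 per arm.

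The Outcome variables section describes different tests. The improvement from t0 to t1 is compared across the three arms with a Kruskal-Wallis test. If that is significant, a post-hoc "Mann-Whitney U test will be applied to reveal which groups (CIMT, BATRAC, or DMCT) differ significantly from each other". No significance level is attached to the pairwise tests there.

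**The concern.** The sizing formula is for comparing two means with normal quantiles. The analysis is rank-based, on small groups, and passes through a three-group test first. Both the small sample and the change of test reduce power relative to the formula, so the stated 80% may not describe the trial's own analysis.

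Two further points determine how large the gap is. One is how many patients per arm will be analysed, since two drop-out figures are given. The other is the level at which pairwise results will be judged. The main hypotheses in the Background (each of modified CIMT and modified BATRAC better than DMCT) are pairwise claims. A pairwise p-value between 0.017 and 0.05 would count as significant under one reading of the article and not under the other.

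**Working it through.** **Inputs, all from the Power analysis section unless noted.** Two-sided alpha 0.017; power 0.80; difference 6 (squared, 36); variance 26 (SD 5.10); equal allocation; 60 recruited (Abstract, Recruitment), so 20 per arm.

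**1. Reproducing the plan's figure.** The quantiles are 2.387 and 0.842, and (2.387 + 0.842)² is about 10.42 (stated 10.43). Then n = 2 × 10.43 × 26/36 = 15.07, given as 15. The z-test power at 15 per group is Φ(√(15 × 36/(2 × 26)) − 2.387) = Φ(3.223 − 2.387) = 79.8%. The figure therefore reproduces as a z-test, apart from the trivial rounding down.

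**2. Same inputs, t-test.** With the noncentral t distribution at two-sided 0.017, power is 74.9% at 15 per group, 78.3% at 16 and 81.3% at 17.

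**3. Same inputs, planned tests.** This was simulated with at least 20,000 runs per setting: normal changes with variance 26, Kruskal-Wallis at 0.05, then Mann-Whitney for a pair that truly differs by 6. The 0.05 for the first test is taken from the headline alpha. The patterns of arm means were (0, 6, 6), (0, 0, 6) and (0, 3, 6).

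| Analysed per arm | Mann-Whitney at 0.017 after the first test | Mann-Whitney at 0.05: one or both active arms 6 above DMCT | Mann-Whitney at 0.05: effects 6, 3, 0 |
|---|---|---|---|
| 15 | about 70% | about 82% | about 76–77% |
| 17 | about 77–78% | about 87–88% | about 81–82% |
| 18 | about 80–81% | about 89% | about 85% |
| 20 | about 85–86% | about 93% | about 89% |

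At 0.017 the pattern of means hardly matters. Rounding the changes to whole points makes almost no difference. Exact Mann-Whitney p-values at 15 per group, without the first test, give 72%. Allowing for such variants, the fair ranges at 0.017 are 70–72% at 15 per arm and 75–78% at 17.

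**4. Drop-out.** 15/(1 − 0.25) = 20 per arm, or 60 in total, which matches recruitment. 15/(1 − 0.15) = 17.6, so 18 per arm, or 54 in total, which does not. Working the other way, 20 × 0.75 = 15 and 20 × 0.85 = 17 analysed per arm. Reaching 18 of 20 requires losses of no more than 2/20 = 10%, which is below both stated figures.

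**5. Does a significant Kruskal-Wallis test protect pairwise tests at 0.05?** With three groups, any two pairwise null hypotheses together imply that all three groups are equal. The only joint hypothesis to test first is therefore the overall one. Kruskal-Wallis at 0.05 followed by pairwise tests at 0.05 is thus a closed test, with strong control at 5%. Simulation gave a familywise error of 0.046 under the overall null and 0.046 under a partial null.

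**The case against.** The strongest reply is that nothing has been miscalculated. The standard normal-approximation formula was used correctly, and planning with it is common. That stands: this is a mismatch between the sized test and the planned test, not an arithmetic error.

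It can also be said that 70% needs both the largest drop-out and the stricter level. This stands in part. With all 20 per arm analysed, power at 0.017 is 85–86%. At 0.05 after the first test it is about 82% even at 15 per arm when one or both active arms differ from DMCT by 6, which is close to the trial's hypothesis. But at 0.017, the only pairwise level the article gives, neither analysed size implied by its drop-out figures reaches 80%.

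Three stronger readings are tempting, and the article does not support them.

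- **The drop-out figures contradict each other.** The second is worded as an upper bound, which 15% satisfies. What remains is that the opening sentence ties the number of patients to 15%, while only 25% produces 60.
- **The pairwise level differs between sizing and analysis.** The analysis paragraph is silent, so there is no conflict, and carrying 0.017 forward is a natural reading. Using 0.017 after a significant first test is conservative but valid.
- **The variance of 26 is the wrong variance.** The label does not exclude the variance of change. Larger SDs would lower power sharply, but any such SD would be the reader's assumption, not a figure in the article.

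**Conclusion.** The point holds in limited form. The stated 80% belongs to a z-test that the trial does not plan to run. For the planned tests at the sizing alpha of 0.017, the shortfall is about 8–10 percentage points at 15 analysed per arm and about 2–5 points at 17. It disappears at about 18 or more per arm. It also largely disappears if the pairwise tests are run at 0.05 after a significant Kruskal-Wallis test; what is left is the 6, 3, 0 pattern at 15 per arm, at about 77%.

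These figures assume a true 6-point difference, variance 26 for the analysed change, normal changes with equal variances, and a Kruskal-Wallis level of 0.05. A reader might infer that the trial is too small or its analysis invalid; neither follows. The recruitment target and the planned tests can stand. What needs correcting is the power statement, and the pairwise level should be fixed before data are seen because it is the decision rule for the main comparisons.

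**What to change.** Keep 60 patients and reword two places.

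1. **Power analysis: drop-out.** Use one planning figure and show the resulting number analysed per arm: 15 at 25%, or 17 at 15%.
2. **Power analysis and Outcome variables: pairwise level.** Choose one option and state it in both sections.
   - *Option A:* Mann-Whitney tests at 0.05, only after a significant Kruskal-Wallis test at 0.05, described as a closed test for three groups. State power of about 82% at 15 and 87% at 17 per arm if one or both active arms differ from DMCT by 6, and about 77% and 81% for effects of 6, 3 and 0.
   - *Option B:* Keep 0.017 for the post-hoc tests and state power of about 70–78% across the two analysed sizes.
3. **Minor clarification.** State whether 26 is the variance of the t0-to-t1 change, and write power 0.80 where the text now says beta.

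The cost is a rewritten power paragraph and one sentence on the pairwise level. Under option B the published power becomes less favourable. Neither option changes recruitment, assessments or the planned tests.

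### The 15 patients per group said to give 80% power come from a normal z-formula; for the planned pairwise rank test, with normal changes, 15 give about 71–72% and about 18 are needed.

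*Protocol article*

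**What the plan says.** The Power analysis section announces a "statistical power of 80% (preventing Type II error" "with an alpha of 5% (preventing Type I error", and then works at a smaller level, "assuming an alpha of 0.017, corrected for multiple testing with 3 groups". Its other inputs are a multiplier (the squared sum of the two normal quantiles) of 10.43, "σ2 (expected variance of sample on ARAT) = 26", "Δ2 (assumed difference in favour ARAT) = 36" and equal group sizes. It concludes that 15 patients per group are needed before drop-out. It gives two drop-out figures: 15% in its opening sentence and less than 25% beside the 15. The Recruitment section sets the total at 60, which is 20 per group.

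The Outcome variables section says "Non-parametric statistics for independent samples will be used". The change in ARAT from t0 to t1 is compared across the three groups with a Kruskal-Wallis test. If that is significant, Mann-Whitney U tests show which groups differ. No significance level is given there for the pairwise tests.

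**The concern.** The formula behind the 15 is that of a two-sample z-test with known variance. The planned pairwise comparison is a Mann-Whitney test. In large samples at a conventional level the two would differ little. With about 15 per group and a level of 0.017 they can differ by several points, because the z-formula ignores both the estimation of the variance and the efficiency of ranks relative to a normal-theory test.

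At stake is how a null pairwise result is read. The Discussion calls for a trial with sufficient power. If true power for a 6-point difference is nearer 71% than 80%, the chance of missing such a difference is about 29%, not 20%. The paragraph also implies that 60 patients can lose up to a quarter and still keep 80% power.

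**Working it through.** **Inputs** (all from the Power analysis section unless noted): difference 6 (squared, 36); variance 26, so SD = √26 = 5.10; standardised difference 6/5.10 = 1.177; two-sided alpha 0.017; power 80%; ratio 1; 60 recruited (Recruitment section). The text calls 0.80 a beta, but the multiplier is reproduced only if 0.80 is the power. One assumption is added: normally distributed changes, as in the plan's own formula.

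**1. The plan's own figure.** The normal quantiles are 2.387 (at 0.9915) and 0.842 (at 0.80). The square of their sum is about 10.42, against 10.43 printed.

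n = 2 × σ² × multiplier / Δ² = 2 × 26 × 10.43 / 36 = 15.07, printed as 15.

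The z-formula power at exactly 15 is Φ(1.177 × √7.5 − 2.387) = Φ(0.836) = 79.8%. Rounding down therefore costs 0.2 points.

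**2. Power of real tests at the same inputs.** The t-test figures use the noncentral t distribution with 2n − 2 degrees of freedom. The Mann-Whitney figures are simulated with exact p-values and a level of 0.017.

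| Completers per group | z-formula | t-test | Mann-Whitney |
|---|---|---|---|
| 15 | 79.8% | 74.9% | 72% |
| 16 | 82.7% | 78.3% | 76% |
| 17 | 85.2% | 81.3% | 78% |
| 18 | 87.4% | 84.0% | 81% |
| 20 | 90.9% | 88.4% | 86% |

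With large-sample instead of exact p-values, Mann-Whitney gives 70.0% at 15, about 75% at 16 and 77–78% at 17. Scores rounded to integers give 70–71% at 15.

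**3. The Kruskal-Wallis gate.** Requiring Kruskal-Wallis at 5% first, then Mann-Whitney at 0.017, gives 71–72% at 15, about 78% at 17 and 80–81% at 18. The gate hardly matters. Kruskal-Wallis alone at 15 per group has 88.5% power if one group differs by 6 from the other two, and 77% if the means are 0, 3 and 6. It does not show which groups differ.

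**4. Distribution shape.** With the same variance and shift, Mann-Whitney at 0.017 and 15 per group gives: uniform 66%, normal 72%, logistic 77%, moderately skewed gamma 78%, t with 5 degrees of freedom 81%, Laplace 82%, and a more skewed gamma (shape 2) 82–83%.

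**5. Pairwise level.** If pairs were tested at 5% after the gate, power at 15 would be about 82%, or 76% if the third group lies midway.

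**6. Drop-out.** At 25%, 15 / 0.75 = 20 per group, which matches the 60 recruited. At 15%, 15 / 0.85 = 17.6, or 18 per group and 54 in all. Read forward, 20 per group leave 20 × 0.85 = 17 completers at 15% drop-out (about 78%) and 20 × 0.75 = 15 at 25% (about 71%). Eighteen completers per group (54 of 60) correspond to 10% drop-out.

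**The case against.** A good deal can be said for the plan.

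- **The sum is not wrong.** The printed 15 reproduces. A reader might infer an arithmetic error from 15.07 being rounded down, but that accounts for only 0.2 points. The issue is the choice of approximation. This stands.
- **Normality is not given by the document.** The plan chooses rank tests, and heavy-tailed or skewed changes with the same variance would bring Mann-Whitney power at 15 to 80% or above. This also stands. So 71–72% and 18 are conditional figures and should be printed with their assumption. Normality is nevertheless the assumption in the plan's own formula, and nothing in the section relies on a heavier-tailed shape.
- **The pairwise level is not fixed where the tests are described.** At 5% after the gate, power at 15 could be about 82%. True, but the Power analysis section uses 0.017 and calls it a correction for three groups, so that is the natural reading.
- **The practical effect is small.** At 20 per group, power is about 86%. At the stated 15% drop-out it is about 78%. The 71% arises only at the 25% ceiling. A reader might infer that 60 patients are too few or that the trial is badly underpowered; the documents do not support that.
- **Planning uncertainty is comparable.** An SD of about 4.65 to 4.7 instead of 5.10 would restore 80% at 15 under the same test. This limits the precision of the figures, but the plan states 26 and should report the power that 26 implies.

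**Conclusion.** The point holds in a limited form. The claim that 15 completers per group give 80% power is not true of the planned pairwise test on the plan's own inputs. With normal changes and a two-sided level of 0.017, 15 give about 71–72% with or without the Kruskal-Wallis step, 17 give 77–78%, and about 18 are needed. The shortfall is not only a matter of ranks: a t-test at 15 has 75%, and passes 80% only at 17.

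In the expected case (15% drop-out) the gap is about two points; at the 25% ceiling it is about nine. The conclusion takes the 6 points, the variance of 26 and the level of 0.017 as given. It moves with the distribution shape (about 66% to 83% at 15) and with the pairwise level. It is a misstatement of power to correct, not a reason to enlarge the trial.

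**What to change.** Keep 60 patients and the planned tests. In the Power analysis section, replace the statement of 15 per group with wording such as:

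> Assuming normally distributed changes and a pairwise Mann-Whitney test at two-sided alpha 0.017, about 18 completers per group are needed for 80% power. Randomising 20 per group gives about 78% power at 15% drop-out (17 completers) and about 71% at 25% drop-out (15 completers). With 15 completers, power ranges from about 66% to 83% for other distribution shapes with the same variance.

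Then make two consistency edits. Give one expected drop-out figure in place of the two now printed, and keep only the matching power. In the Outcome variables section, state the level for the post-hoc Mann-Whitney tests; if it is not 0.017, quote the power for the level chosen.

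The cost is one reworded paragraph, one added phrase and a slightly less favourable stated power. No further patients are needed.
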